#### Feedback

A feedback section then asks participants to rate the quality of the session on a 6-point German school-grade scale (very good – good – satisfactory – sufficient – unsatisfactory – insufficient) and provide written additional feedback if they wish.

At the end of the session, participants are asked to regularly complete their activity calendars (see below), an appointment for the following booster session via computer-assisted phone-based intervention is scheduled, participants are thanked and dismissed.

##### PrevOP-PAP-I computer-assisted phone-based interventions (weeks 3, 27, 50, and 52 following T0)

Throughout the following 12 months (Fig. 3), four computer-assisted phone-based interventions are scheduled as booster sessions of the main face-to-face intervention session (T1) described above. Participants are called by study staff at pre-scheduled appointments and are guided through the booster interventions over the phone. Study staff follow a computer-based structured intervention and record participants’ responses in a computer program displayed in a browser. Earlier responses from participants’ face-to-face computer-assisted intervention or earlier computer-assisted phone-based interventions are fed back into the new session. All four phone-based interventions are nearly identical (except for varying time frames since the last intervention session and addenda in phone-based interventions 3 and 4) and designed to boost participants’ planning, self-efficacy, and action control regarding their regular PA. The phone-based interventions 3 and 4 have an additional component of network creation, i.e., during phone-based intervention 3, participants are prompted to find a sports companion to be active with them on a regular basis and during phone-based intervention 4, they are asked to include the sports companion into their action plans. Behavior change techniques (BCTs; [13]) used in phone-based interventions are provided in brackets following a brief description of intervention sections described below.

#### Introduction

Following initial greetings, a brief conversation on how the participant fared since the last contact, and a brief introduction into the purpose and structure of the phone-based intervention session are given. Participants are then asked to fetch activity calendars that they completed during the past two weeks (phone-based interventions 1, 2, and 4) as well as two new activity calendars that have been provided before (see below) as support material for the session. Participants are then generally asked how they fared with their most-recently completed activity calendars and implemented PA goals during the past two weeks (phone-based interventions 1, 2, and 4).

#### Goal/plan review

Following this general assessment of the PA goals for the past two weeks, each goal set during the past intervention session is reviewed. Participants are read their past PA goal and their matching action plan and asked how successful they have been in implementing this plan (in %). Patients are instructed to refer to their past two-week activity calendars to produce an estimated percentage of their goal attainment. They are then asked to recollect positive experiences they have had when implementing their action plan. Then participants are asked whether they want to continue with this particular PA goal and/or action plan for the next weeks or whether they want to change it/them. If participants want to change their PA goal, they are asked which other activity they would like to carry out. They are then asked to form a new action plan, following an “If/When.., then…” structure. Then participants are asked to indicate on a 6-point response scale (not at all true to very true; read to them) their agreement with the following statement (plan execution self-efficacy; [46]): “I am sure that I can act as planned in this situation”. Next, participants are instructed to form a new coping plan for the changed activity goal and/or action plan. Again, coping plans are to be framed in an “If…, then…” structure. Changed activity goals, action plans, plan self-efficacy scores, and coping plans are recorded by study staff. If participants do not want to change activities and/or plans, their past entries are kept in the system, but new plan self-efficacy items are completed. At the end of the review of former goals and plans, participants are asked if they want to add new PA goals to their list (up to a maximum of 5 PA goals all in all), in which case the new PA goal, action plan, plan self-efficacy, and coping plan-procedure is then repeated for as many PA goals as are newly set. Participants are then slowly read each action plan (kept, altered, and new ones) and asked to fill them into their new activity calendars. A list of all action and coping plans generated during this session is printed and sent to participants via mail. Participants are then reminded to keep completing their new activity calendars during the next two weeks (BCTs 1.1, 1.3, 1.5, 1.7; [13]).

#### Phone-based intervention 3 addendum -- network creation

At the beginning of this section which follows the above-described goal/plan review section, participants are asked if they have ever engaged in physical activity together with another person. If participants answer in the affirmative, they are instructed to recollect positive experiences with joint physical activity in the past and are asked whether they could imagine to be physically active with another person in the future as well. If participants affirm, they are asked to indicate the initials and the nature of the relation to this person (e.g., partner, child, friend, neighbour). If participants negate to have ever engaged in physical activity together with another person in the past, they are asked if they can imagine to be physically active with another person in the future. If participants affirm, they are again asked to indicate the initials and the kind of relation they share with this specific person and are instructed to contact this person and ask them if they wanted to be their sports companion before phone-based intervention 4. If participants negate, this issue is not further explored (BCTs 3.2; [13]).

#### Phone-based intervention 4 addendum -- network creation review

Following the introduction section and before the goal/plan review section, participants who have indicated during the phone-based intervention 3 that they wanted to engage in physical activity with another person are reminded of this and asked if this is still the case and whether it is still the same person. If participants do not want to be active with someone, the same goal/plan review section as described above continues. If participants respond in the affirmative or in case participants now name a new person as a potential sports companion, then this issue is taken up in all following goal/plan reviews. During each goal/plan review, participants are asked to indicate if they want to include their sports companion in this action plan and indicate the sports companion’s initials and in which type of relation they are. Participants are then asked to include in the “then...”-parts of their “If/When…, then...” action plans the persons with whom they want to be active. All information is recorded by study staff (BCTs 1.4, 3.2; [13]).

#### Feedback

A feedback section then again asks participants to rate the quality of the session on a 6-point German school-grade scale (very good – good--satisfactory – sufficient—unsatisfactory – insufficient) and provide additional oral feedback if they wish. Feedback scores and points are recorded by study staff.

At the end of each phone-based intervention-session that lasts between 20 and 60 min, participants are asked if they have any questions, reminded of the next study appointment, reminded to use the learned self-regulatory strategies in their daily lives, and thanked.

##### Activity calendars (weeks 1 to 4, weeks 25 to 28, weeks 50 to 53 following T0)

Participants are provided with printed sets of activity calendars to be taken home and completed daily at the end of the day throughout weeks 1 to 4 (following their face-to-face intervention and phone-based intervention 1), weeks 25 to 28 (surrounding phone-based intervention 2), and weeks 50 to 53 (following phone-based intervention 3 and interspersed with phone-based intervention 4) following T0 (Fig. 3). Activity calendars provide written instructions on the top and are depicted in form of tables with columns for 7 days. Columns and column headers are blank for participants to fill in the date and days of the week in column headers and their created action plans for each day during the face-to-face or phone-based interventions. Filled-in plans can be abbreviated, but shall minimally contain the situational cues to trigger action, what participants are planning to do, and for how long (e.g., Tuesday-column: “after breakfast, go swimming, 25 minutes”). Next to each day column there is a narrower column where participants are instructed to put a checkmark next to their action plan if they have implemented their plan on a given day. At the bottom of the calendar section there is an additional field where participants can note additional PA bouts pursued during a given day. All calendars and their instructions are identical except for the last two ones to be completed following phone-based intervention 4 (from week 52 following T0). Here, participants are additionally instructed to write down with whom they plan to pursue the planned activity (e.g., after lunch, ride my bike at a good pace, 40 min, with my husband). Calendars are meant to trigger participants’ action control and support their development of self-efficacy by daily review of their mastery experiences. Following the completion of four calendars in a row, participants are asked to either hand them to or mail them back to study personnel, participant codes are noted on the top of each calendar sheet (BCT 2.3, 2.4, 2.7; [13]).

### Benefits and harms

Participants in the PrevOP-PAP-I may benefit from the use of self-regulatory strategies taught in the intervention not only in terms of the uptake and maintenance of regular PA, but also in terms of other volitional activities of daily living (e.g., eating, chores, social activities). Transfer of the use of these strategies is encouraged in the interaction with study staff during intervention sessions. If participants manage to maintain regular PA, they may experience a decrease in OAK symptom severity as well. The PrevOP-PAP-I is not expected to be harmful for participants which is why a data monitoring and safety board or stopping rules are not needed for the PrevOP-PAP trial. Due to data-protection principles, outcomes of the psychological screening instrument Center for Epidemiologic Studies Depression Scale are not individually monitored (see below; note that this version of the scale does not contain an item on suicidal ideation) [47]. Instead, all participants are routinely given information about emergency services they can turn to should they experience psychological problems.

### Data collection and entry

Data are collected over a 2-year period (i.e., participants remain in the study for 2 years) at 6 measurement points (or periods) in time (T0 to T5) by trained study personnel (see Fig. 3). Inter-measurement intervals range from daily to 6 months, depending on the assessment in question. Data are assessed with self-report questionnaires and objective measures (e.g., accelerometers, body weight). Participants schedule assessment sessions at the study center at Charité – Universitätsmedizin Berlin. During assessment sessions, they are handed a questionnaire booklet, asked to complete it during the session and instructed to turn to study staff with questions (T0, T2, T3, T4, T5; T1 is the main intervention session with additional assessments). At T0, T3, and T5 participants undergo further medical examinations and are handed and instructed to wear accelerometers for eight days. At the end of T0, T3, and T5 periods, i.e., following each one-week accelerometer assessment, participants are additionally asked to complete a brief self-report measure on their daily PA during the past week. Completed study materials and accelerometers are either directly returned to study personnel or mailed to the health psychology lab at Freie Universität Berlin. Data entry will be conducted by trained PrevOP-PAP study personnel. Quality management of data entry will include guidance by a data entry manual, regular plausibility checks, and double entry of portions of the assessed data.

#### Primary outcome: OAK symptoms

PrevOP-PAP’s primary outcome are self-reported OAK symptoms assessed with the Western Ontario and Mc Master Universities Osteoarthritis Index (WOMAC; [48]), in its version for OAK. The WOMAC contains 24 items on symptoms of OAK including stiffness, pain, and functional limitations. Participants are asked to respond to items on 11-point numeric rating response scales anchored at “no pain” (0; stiffness or limitation, respectively) and “extreme pain” (10; stiffness or limitation, respectively). The WOMAC has been reported to be reliable and valid [48].

#### Secondary outcomes

##### Physical activity (PA)

Daily PA (in minutes) is measured with tri-axial accelerometer devices (ActiGraph, GT3X) providing information on activity counts. During each assessment period (see Fig. 3), participants are instructed to wear devices strapped around their hips for 8 days, during their waking hours. As devices do not have screens, participants are unable to monitor their PA data on their own. Following assessment periods, data are downloaded from the devices by trained study staff. Using a software program, activity data are then grouped into minutes of PA of different intensities; i.e., light activity, moderate to vigorous physical activity (MVPA), and sedentary behaviors. Data are to be used if participants have worn accelerometers on at least 4 days for at least 10 h a day. In addition to objective assessments of PA, also repeated self-report assessments are conducted using the German version of the Office in Motion Questionnaire ([49]; see Fig. 3) which is complemented by household and work-domain activities as assessed with its predecessor measure (Physical Activity Questionnaire; [50]). The Office in Motion Questionnaire assesses the duration of daily PA of different intensities in the domains of transportation (at work/outside of work), household, work, leisure time, and sports activities during the past week. A sum score of minutes spent in activities of different intensities will be generated. Authors of the instruments reported satisfactory reliability, validity, and change sensitivity for the measures [49, 50].

##### Health-related quality of life and depressive symptoms

Generic health-related quality of life is assessed with a 12-item measure [51]. Additionally, a 1-item visual analogue scale asks participants to rate their pain on the present day [52]. Depressive symptoms are assessed with the 20-item German version of the Center for Epidemiologic Studies Depression Scale [47].

#### Other outcomes and covariates

##### Cognitive and social intervention mechanisms

Most components of intervention mechanisms are derived from the HAPA and serve as further outcomes. Scales are PA-specific and were adapted from Sniehotta et al. (2006) [27], where they showed satisfactory internal consistencies and validity indicators. Unless otherwise noted, response options range from 1 = “does not apply at all”/“very unlikely” to 6 = “applies exactly”/“highly likely”. Motivational intervention mediators include: Risk perceptions (3 items), task self-efficacy (4 items), outcome expectancies (6 items positive, 4 items negative), and intention to be physically active (4 items). Volitional intervention mediators include: Action planning (4 items), coping planning (5 items), maintenance self-efficacy (3 items), recovery self-efficacy (3 items), and action control (6 items).

A network-creation index was modelled after the HAPA’s stage algorithm [27]. Participants are asked to indicate the response that fits them best: (1) I have not yet thought about exercising with someone else (2) I have thought about exercising with someone else, (3) I have thought about exercising with someone else and am looking into this soon, (4) I have already looked for sports companions, but so far have not found one. (5) Right now, I am exercising with someone. (6) Right now, I am not exercising with anyone any longer. If participants are active with other persons, they are asked to indicate their relations with them and identify them by their initials. Additionally, collaborative action planning (3 items) and collaborative coping planning (3 items) with potential sports companions are assessed. Items are modelled after those of individual planning, only they refer to the target person and the sports companion.

Additional social exchange strategies with important or close others, that may or may not be identical with the sports companion are also assessed. Before participants respond to social exchange strategy items, they are asked to indicate the relationship to and initials of the important or close person they refer to (“significant other”). Social exchange strategy items were adapted from Burkert et al. (2011) and Knoll et al. (2017) [31, 32], where they showed satisfactory psychometric properties. All assessed information refers to the identified significant other as a source or provider of social exchange and is specific to the domain of PA: Dyadic action planning (4 items), dyadic coping planning (5 items), mobilized social support (4 items), received social support (6 items), and received social control (6 items). Response options range from 1 = “does not apply at all”/“very unlikely” to 6 = “applies exactly”/“highly likely”.

##### Beliefs and attitudes

A number of self-regulatory beliefs are also assessed. Sources of self-efficacy are assessed with a scale by Warner et al. (2014) [53]. This scale assesses mastery experiences (2 items), vicarious experiences (2 items), symbolic experiences (4 items), and physiological states (4 items) [17]. Additionally, a 3-item measure of attitudes towards exercising with others was developed. Exercise autonomy (4 items), competence (4 items) and relatedness (4 items) is assessed with a measure by Vlachopoulos and Michailidou (2006) [54]. Beliefs about willpower are assessed with a 12-item measure by Job, Walton, Bernecker, and Dweck (2013) [55]. Again, response options range between 1 = “does not apply at all” to 6 = “applies exactly”.

##### Additional information and socio-economic variables

Additional information about participation in other PA programs or sports clubs (3 items), dieting (1 item; “Are you currently on a diet to lose weight?”) and/or participation in commercial diet programs (3 items) is assessed by asking patients whether this is the case (yes/no), which program they attend, and for how long they have been attending (years and months). Alcohol consumption is assessed by asking participants to estimate the number of standard servings of alcohol consumed per week. Smoking is assessed by four items adapted from Ochsner et al. (2015) [56]. Height and weight are assessed objectively as part of the medical examination in the PrevOP-MMT. Additionally, the following socio-economic variables are assessed: Sex, age, marital status, number of children, living arrangements (alone vs. with others), school education, professional training, employment status, monthly net income, nationality, and native language.

### Statistical analyses

#### Randomization check, manipulation check, drop-out analyses, and intention to treat

A randomization check will address equal distributions of all baseline measures of all outcomes and covariates across conditions using multivariate analyses of variance and chi-square tests for nominal and ordinal-scale baseline data. Manipulation checks of intervention strategies will test differential intra-individual increases of cognitive and social variables targeted with the different intervention modules. For this, 2-level mixed models with TIME as a within-subjects factor and condition (PrevOP-PAP-I; PrevOP-PAP-CTRL) as the between-subjects factor as well as their interaction will be fit.

Analyses will be carried out in an intention-to-treat manner. Depending on the analytical approach to the main hypotheses, multiple imputation or full information maximum likelihood strategies will be used to keep information of individuals who were randomized to one of the PAP conditions, but dropped out at any later point of the study, in the analyses. Drop-out analyses will test baseline differences between continuers and non-continuers in all variable groups using *t*-tests, chi-square tests, and logistic regressions. Identified unique differences between continuers and non-continuers (i.e., drop-out mechanisms) will be included in the imputation model (along with this study’s central variables; in case of multiple imputation) or path models (in case of full information maximum likelihood; [57]). Use of either is pre-determined by the statistical approach used to test our hypotheses.

#### Hypotheses tests

Longitudinal mediation analyses will be conducted using manifest path analyses. PrevOP-PAP-condition will be specified as a dummy-coded independent variable, accelerometer-assessed MVPA as a mediator (in minutes per week), and WOMAC scores as the primary outcome (controlling for respective baseline assessment). Dummy-coded PrevOP-MMT-conditions will be routinely tested as moderators of the association between MVPA (mediator) and WOMAC (primary outcome). If no interactions occur, PrevOP-MMT-conditions are tested as simple-effect covariates and dropped only if they are not related to the mediator or primary outcome. Further covariates are determined by results of the randomization check and bivariate correlations of assumed covariates with primary or secondary outcomes. Significance of all indirect effects will be tested using bootstrapping methods.

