#### Primary research question

Compared to an active control condition, can a theory-based psychological adherence program designed to increase self-regulation and network formation facilitate the uptake and maintenance of regular PA (key secondary outcome) and contribute to a reduction in symptom severity (primary outcome) in persons with moderate OAK?

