### Power analysis

For the PrevOP-MMT a sample size of *N* = 240 has been determined. For the PrevOP-PAP, choosing an alpha level of .05 and a stability factor of .68 of the WOMAC (www.rheumatology.org), a minimum sample size of *n* = 122 is required which includes 2 groups at 5 points in time up to the primary endpoint (baseline to 24 months) to detect a small effect (*f* = 0.1) of a within by between subjects factors interaction with a power of .95. With an expected drop-out rate of 20%, the required sample size increases to *n* = 153. This required sample size for the PrevOP-PAP trial is thus in accord with the PrevOP-MMT-required inclusion of *N* = 240 participants.

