#### Additional analyses

Additional 2-level mixed model analyses will be used to examine intra-individual change (within-person) in primary and secondary outcome variables as a function of study conditions (between-person). Analyses using available self-report PA data will benefit from a larger number of - and more tightly-spaced assessments.

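### The designated hypothesis test is the indirect effect through MVPA, while the randomised WOMAC comparison that was powered is ranked as an additional analysis

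*Protocol article*

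**What the plan says.** The *Primary research question* opens with "Compared to an active control condition, can a theory-based psychological adherence program" and goes on to ask whether the programme can raise physical activity (named there as key secondary outcome) and "contribute to a reduction in symptom severity (primary outcome) in persons with moderate OAK". *Primary outcome: OAK symptoms* confirms the outcome: "PrevOP-PAP’s primary outcome are self-reported OAK symptoms assessed with the Western Ontario and Mc Master Universities Osteoarthritis Index".

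The section *Hypotheses tests* begins "Longitudinal mediation analyses will be conducted using manifest path analyses". Condition is the independent variable, with "accelerometer-assessed MVPA as a mediator (in minutes per week), and WOMAC scores as the primary outcome (controlling for respective baseline assessment"). It ends "Significance of all indirect effects will be tested using bootstrapping methods". No test of the total or direct effect of the programme on WOMAC is named there.

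The between-condition analysis of WOMAC appears under *Additional analyses*, where the protocol writes: "Additional 2-level mixed model analyses will be used to examine intra-individual change (within-person) in primary and secondary outcome variables". Study condition is the between-person factor, but the sentence names neither the PAP contrast nor a time point.

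*Power analysis* works with two groups, five occasions up to 24 months and a group-by-time interaction, "choosing an alpha level of .05 and a stability factor of .68 of the WOMAC", f = 0.1 and power .95. It arrives at n = 122, or 153 after 20% drop-out.

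**The concern.** The order of the analyses does not match the question or the sample size. Randomisation protects two things here: the effect of the programme on MVPA and its total effect on WOMAC. It does not protect the association between MVPA and WOMAC. People whose knees hurt less may move more, and common causes may drive both. Adjusting for baseline does not remove symptom changes that occur after baseline.

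Two errors follow if the designated test decides the conclusion. Symptom reduction could be claimed although the arms have the same WOMAC scores, or although a gain through MVPA is cancelled by harm through another route. Conversely, a real reduction could be missed because it does not pass through accelerometer MVPA. Such routes are plausible on the protocol's own account: the *Background* lists strengthening exercise as a separate target, and the *Discussion* concedes that hip-worn devices do not capture activities such as cycling.

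**Working it through.** **1. Which test was powered?** Inputs from *Power analysis*: f = 0.1, k = 2 groups, m = 5 occasions, ρ = .68, α = .05. Sphericity is assumed.

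- Noncentrality λ = f²·N·m/(1 − ρ) = 0.01 × 122 × 5 / 0.32 = 19.06.
- df1 = (k − 1)(m − 1) = 4; df2 = (N − k)(m − 1) = 120 × 4 = 480.
- Power at N = 122 is 0.953. At N = 120 it is 0.9499, so 122 is the smallest even N that reaches .95.
- Drop-out: 122 / 0.8 = 152.5, rounded up to 153.

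Both stated figures reproduce. With 240 × 0.8 = 192 analysed, the same interaction has power 0.997. The powered test is therefore the group-by-time comparison of WOMAC. No power is given for the indirect effect.

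**2. Can the indirect effect be significant with no effect on WOMAC?** This was simulated with 192 analysed and WOMAC correlation .68. Everything else is an assumption, because the protocol gives no path values: the programme raises MVPA by 0.4 SD; MVPA stability is .5; current symptoms lower MVPA with coefficient −0.1 to −0.3; neither the programme nor MVPA affects WOMAC. The indirect effect is tested by joint significance of its two paths, adjusted for baseline MVPA and baseline WOMAC. The total effect is tested by baseline-adjusted comparison of 24-month WOMAC.

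| Test | Rejection rate |
|---|---|
| Indirect, MVPA at T3 (12 months) | about 6–46% |
| Indirect, MVPA at T5 (24 months) | about 18–89% |
| Randomised total effect | about 5% |

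With a symptom coefficient of 0, the indirect test rejects in about 4%. Letting MVPA stability run from 0 to .7 widens the ranges to about 4–65% (T3) and 14–97% (T5). With a programme effect on MVPA of only 0.2 SD (coefficient −0.3, stability .5), the rates are 9% and 34%.

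**3. Other patterns.** A simpler simulation used n = 192, no baseline covariates, a Monte Carlo interval for the product of the paths, and assumed paths in units of the residual SD.

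| Scenario | Indirect significant | Total significant |
|---|---|---|
| MVPA raised by 0.5, no effect on WOMAC, unmeasured common cause (loading 0.55) | 92% | 4.9% |
| Same, without the common cause | 4.9% | 5.8% |
| WOMAC lowered by 0.5 by a route other than MVPA | 5.3% | 89% |
| Indirect benefit of 0.15 offset by direct harm of 0.15 | 92% | 5.8% |

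**4. Power of a single 24-month contrast.** With 96 per arm and baseline adjustment, the standard error in SD units is √(1 − .68²) × √(2/96) = 0.733 × 0.144 = 0.106. Power ≈ Φ(d/0.106 − 1.96), which gives 0.47, 0.81 and 0.97 for assumed differences d = 0.2, 0.3 and 0.4 SD. The stated .95 does not carry over to this contrast.

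**The case against.** The strongest reply is that the randomised comparison is already there. The mixed model under *Additional analyses* covers the primary outcome by study condition, the protocol commits to intention-to-treat analysis, and the trial was sized on that interaction. This stands. A reader might infer that no randomised test of WOMAC is planned, or that randomisation leaves the primary question unanswered. The documents do not support either reading. What is wrong is the rank of the comparison.

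Second, mediation is a declared aim. The Abstract expects fewer symptoms as a consequence of maintained activity, and *Aims and primary research question* describes activity as the behavioural predictor of reduced symptoms. This also stands and is a reason to keep the path model. It does not make the indirect effect an answer to a question posed against a control arm.

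Third, the path model contains a direct path, and a total effect could be derived from it. That is true, but no test of either is planned.

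Fourth, the rejection rates depend on chosen inputs, and the highest pair 24-month MVPA with 24-month WOMAC. The analysis is described as longitudinal and MVPA is measured only at T0, T3 and T5, so T3 MVPA with T5 WOMAC is the more natural reading, although the section does not fix the wave. The direction survives across these choices; no single rate should be quoted as the size of the problem.

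**Conclusion.** The concern holds as a conflict of ranking. The *Hypotheses tests* section designates a test that randomisation does not fully protect, while the comparison that answers the primary question and determined the sample size is labelled additional. Following that order can lead to a wrong primary conclusion in either direction.

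The inflation (about 6–46% with 12-month MVPA and 18–89% with 24-month MVPA, against a nominal 5%) is illustrative. Of the correlations and path values behind it, only the .68 comes from the protocol. If symptoms do not influence activity and there is no common cause, the indirect test keeps its level.

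**What to change.** Make the intention-to-treat PAP-I versus PAP-CTRL comparison of WOMAC, from the mixed model already planned, the confirmatory test. Adjust for sex (the randomisation stratum) and MMT arm, and choose one form in advance:

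- **The powered group-by-time interaction**, with WOMAC at T0, T2, T3, T4 and T5 as responses. The existing sample-size statement then applies.
- **The 24-month contrast**, with T2 to T5 as responses and T0 WOMAC as covariate, or with T0 as a response and the arm means constrained equal at baseline. T0 should not be both response and covariate. State this contrast's own power: about 0.47, 0.81 and 0.97 for assumed differences of 0.2, 0.3 and 0.4 SD with 96 per arm.

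Make the randomised difference in accelerometer MVPA the key secondary test. Keep the path model as an explanatory analysis of the stated mechanism, and say that symptom reduction will not be claimed from the indirect effect alone.

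The cost is a change of wording and ranking plus, for the second option, a new power statement. No participants, visits or data are added. Mediation loses its headline position, and a single contrast may have less power than the stated .95.
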